#### Data back-up

The primary database will be backed up once per month. At the same time, the data analysis files will also be backed up.

### Statistical methods

#### Dataset analysis

For the primary endpoint of percentage change in LDL-C from baseline, the efficacy of acupuncture and moxibustion will be evaluated at week 12 by comparing the treatment effect to that of the active control group. A type I error of 0.05 will be allocated to the test.

There are three main analysis sets:Full analysis set (FAS): includes all randomized subjects who have received at least 1 investigational treatmentCompleter Analysis Set (CAS), includes subjects in the FAS who completed their scheduled intervention and have a nonmissing LDL-C value at week 12Effect Durability Analysis Set (EDAS), includes subjects in the FAS who completed their scheduled intervention and have non-missing LDL-C values at week 6 and week 12

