### Hypotheses and objectives

#### Hypotheses

Warm needling acupuncture and medicinal cake-separated moxibustion (short as “acupuncture and moxibustion” in the following text) is noninferior to active control, in subjects with hypercholesterolemia, on° percent change of LDL-C° absolute change of LDL-C° percent change of HDL-C° percent change of TC° percent change of TG° rate of subject achieving LDL-C goal
Acupuncture and moxibustion is superior to active control, in subjects with hypercholesterolemia, on safety and tolerability° Adherence

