### Trial design

This is a multicenter, open-label, randomized, stratified, active-controlled, noninferiority trial with two parallel groups. Randomization will be performed with a 1:1 allocation. Subjects with LDL-C values above the recommended level who meet the inclusion/exclusion criteria will be stratified based on their risk levels of heart disease [19, 20]. Then, they were instructed to follow the NCEP Adult Treatment Panel (ATP) [20] Therapeutic Lifestyle Change (TLC) diet first. After TLC is completed, subjects who have not reached the target lipid level will be randomly assigned to the treatments of either acupuncture and moxibustion or simvastatin. The duration of treatment for this study will be 12 weeks, followed by another 4 weeks for post-treatment assessment.

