#### Acupuncture and moxibustion versus simvastatin

According to the re-assessment of fasting lipid after TLC, a decision will be made on whether the lipid level has arrived at the target level (see Table 5 in Appendix 1) and whether subjects should continue with the intervention. For those who have not reached the target lipid level, they will be randomized in equal proportions between “acupuncture” and “simvastatin.”Acupuncture and moxibustionRationale for treatment:Warm-needling acupuncture and medicinal cake-separated moxibustion will be applied in the study which is guided by the approach of Traditional Chinese Medicine (TCM). The cake-separated moxibustion treatment belongs to the category of indirect moxibustion which applies moxibustion, herb and acupoints together. In this treatment, a drug-cake mixture is allocated upon selected acupoints, and then the lit moxa cone is placed onto the cake. In this case, the moxa-effect enhanced by the active components of the drug cake is allowed to penetrate through the skin and the acupoints.Based on the TCM theory that the heart is in charge of the blood circulation and blood vessels, some specific acupoints related to heart meridian and heart are selected, such as the *Shu* acupoint (RN14) and the *Mu* acupoint (BL15) of the heart meridian. BL18, BL20 and BL23 are used to tonify the spleen *Qi*, strengthen the liver *Qi* and also maintain the kidney *Qi*, as well as facilitate the conversion of lipids in the liver. ST40 and ST25, which belong to the stomach meridian and help the transformation function of spleen, can protect and work against hyperlipidemia by assisting the removal of phlegm from the body.Additionally, five Chinese herbal medicines are selected, including *Salviae Miltiorrhizae Radix* (*Dan shen*), *Crataegi Fructus* (*Shan zha*), *Curcumae Radix* (*Yu jin*), *Rhei Radix et Rhizoma* (*Da huang*), and *Alismatis Rhizoma* (*Ze xie*). They are able to activate the blood circulation, remove blood stasis and pain, clear away heart fire, remove irritability, nourish the blood and calm down the mind.In clinical practice, several studies with small sample sizes have assessed a variety of acupoint prescriptions, medicinal cake ingredients, treatment duration, etc. [12, 16]. Among these studies, Li et al. applied warm needling acupuncture on acupoints such as *Fenglong* (ST40, bilateral), *Zusanli* (ST36, bilateral), etc., once a day for 35 days, over a period of 12 weeks, showing a significant decrease in LDL-C, noninferior to statins [12]. Li et al. applied medicinal cake-separated moxibustion on two groups of acupoints, alternating over a period of 40 days with each group receiving 20 times of intervention [16]. This study demonstrated a remarkable decrease in LDL-C and TC, superior to the effect of a placebo. Meanwhile, Chang et al. have also examined effects of medicinal cake-separated moxibustion with different dosage upon blood fat and hemorheology in patients with hyperlipemia, showing that three moxa cones and five moxa cones both have therapeutic effect [17]. With these studies, so far we know, warm-needling acupuncture and cake-separated moxibustion are both effective for hyperlipidemia, respectively. Together with our previous clinical experiences on treating hyperlipidemia, we selected the studies mentioned above as pilot studies of this trial in determining the procedure course of the intervention.Needling/moxibustion details (demonstrated in Table 1)Treatment regimen:Interventions of warm-needling acupuncture and medicinal cake-separated moxibustion will be split into two groups. Group 1 (warm-needling acupuncture and medicinal cake-separated moxibustion) and group 2 (medicinal cake-separated moxibustion only) will alternate by week over the administration period (shown in Fig. 2), in order to avoid fatigue and nonresponse of acupoints due to constant stimulationPractitioners: registered acupuncturists who have completed post-secondary education on acupuncture, practiced acupuncture for more than 3 years, and passed the national qualification exam for Chinese medicine doctors

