### Sample size

A significance level of 0.95 and a power of 0.80 will be allocated for the calculation of sample size. In accordance with a previous study [17], we could employ an effect size of 0.343 on absolute value change of LDL-C value, and a standard deviation of 0.7. In this case we estimate that the sample size for the acupuncture group and active control group should be approximately 65, respectively. The total sample size needed is 130.

In case of missing observation and patients lost, we assume that 90% of subjects will remain in the study. Thus, the sample size for two groups should be roughly 70 for each group.

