#### Statistical analysis plan

The primary analysis set for the primary endpoint is the FAS. It is to use the repeated measures, linear mixed-effects model, including terms for treatment group, stratification factor, baseline LDL-C, scheduled visit and the interaction of treatment with scheduled visit. Missing values will not be imputed when the repeated measures, linear mixed-effects model is used.

We will use the chi-squared test for binary outcomes, and the *t* test for continuous outcomes. For subgroup analyses, we will use regression methods with appropriate interaction terms (respective subgroup treatment group). Multivariable analyses will be based on logistic regression for binary outcomes and linear regression for continuous outcomes. We will examine the residual to assess model assumptions and goodness-of-fit. For timed endpoints, such as mortality, we will use the Kaplan-Meier survival analysis followed by the multivariable Cox proportional hazards model for adjusting for baseline variables. We will calculate Relative Risk (RR) and RR Reductions (RRR) with corresponding 95% confidence intervals to compare dichotomous variables, and difference in means will be used for additional analysis of continuous variables. *P* values will be reported to four decimal places with *P* values < 0.05 reported as *P* < 0.05. Up-to-date versions of R (R Foundation) will be used to conduct analyses. For all tests, we will use two-sided *P* values with alpha no greater than 0.05 level of significance. We will use the Bonferroni method to appropriately adjust the overall level of significance for multiple primary outcomes, and secondary outcomes.

In investigation of the robustness of the analysis results, the primary analysis will be repeated using the CAS. In addition, parametric analysis of covariance (ANCOVA) and appropriate nonparametric methods will be used on the FAS, in which missing data will be imputed using the last-observation-carried-forward (LOCF) approach. The primary analysis will also be repeated for subgroups of interest.

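### The trial is declared noninferiority, but the protocol states no margin and no rule comparing a confidence limit with one; its stated inference is two-sided P values at 0.05

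*Protocol article*

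**What the plan says.** The Trial design section states: "This is a multicenter, open-label, randomized, stratified, active-controlled, noninferiority trial with two parallel groups". Under Hypotheses, the intervention "is noninferior to active control, in subjects with hypercholesterolemia" on six efficacy outcomes, the first being percentage change in LDL-C. Safety and tolerability, and adherence, are listed there as superiority hypotheses.

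For the primary endpoint, the Dataset analysis section says that "the efficacy of acupuncture and moxibustion will be evaluated at week 12 by comparing the treatment effect to that of the active control group", and adds: "A type I error of 0.05 will be allocated to the test". The Statistical analysis plan section names a repeated-measures linear mixed model on the full analysis set, repeats it in the completer set, mentions t and chi-squared tests, and requires for all tests two-sided P "values with alpha no greater than 0.05 level of significance". Confidence intervals are mentioned for relative risks and, under Consistency analysis, for week 6 against week 12. None is tied to a noninferiority decision. The Data monitoring section has the committee advise when the intervention is shown to differ from control.

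The Sample size section says: "In accordance with a previous study [17], we could employ an effect size of 0.343 on absolute value change of LDL-C value", with a standard deviation of 0.7 and power 0.80, giving about 65 per arm.

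**The concern.** A noninferiority claim needs a margin and a rule: the confidence limit on the unfavourable side must exclude a deficit as large as the margin. A P value for the null hypothesis of no difference does not do this. If it is significant, it shows a difference; if it is not, it says little about how much worse the new treatment could be. As written, the plan has no step that turns the week-12 comparison into a yes or no on noninferiority.

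The gap leaves room for two bad outcomes: a nonsignificant result presented as noninferiority, or a margin chosen once results are known. The first becomes easier as the trial becomes less informative, which is the wrong incentive.

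This goes beyond detail that an article leaves to a fuller document. The margin is part of the hypothesis and of the sample size, and the article itself fixes the model, alpha, sidedness, analysis sets and sample size inputs. Together these do not make a noninferiority test.

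**Working it through.** **Inputs (Sample size section).** Number 0.343 on absolute LDL-C change, unit not given; SD 0.7; power 0.80; 65 per arm. The stated significance level of 0.95 is read as alpha 0.05.

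**1. Reproduce the plan's figure.**
- Difference to detect, two-sided 0.05: n = 2 × [SD × (1.960 + 0.842) / 0.343]² = 2 × [0.7 × 2.802 / 0.343]² ≈ 65.4, so 66 per arm against 65 stated.
- Margin 0.343, one-sided 0.025, true difference zero: the same formula, so again 66.
- One-sided 0.05 gives 52, and 0.343 read as a standardized effect gives 134. Neither matches.

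The sample size therefore fits a superiority design and a noninferiority design equally well.

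**2. What happens if nonsignificance is taken as noninferiority.**
- SE = 0.7 × √(2/65) = 0.1228.
- True deficit 0.343: 0.343 / 0.1228 = 2.79. P(nonsignificant) ≈ Φ(1.96 − 2.79) = 0.20.
- A rule requiring the upper 95% limit to lie below 0.343 accepts that same deficit with probability Φ(−1.96) = 0.025.
- With 33 per arm, SE = 0.7 × √(2/33) = 0.172, and the 0.20 rises to 0.49.

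**3. Power of 65 per arm as a noninferiority trial.** Absolute scale, true difference zero, power = Φ(margin / 0.1228 − 1.96). Margins other than 0.343 are assumptions.

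| Margin | Power at 65 per arm | n per arm for 80% |
|---|---|---|
| 0.343 | 0.80 | 66 |
| 0.30 | 0.69 | 86 |
| 0.25 | 0.53 | 124 |
| 0.20 | 0.37 | 193 |

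**4. Why 0.343 cannot simply be carried over.** The primary endpoint is percentage change. If the unit is mmol/L (an assumption), 0.343 × 38.67 = 13.3 mg/dL. At the LDL-C goals that separate the three risk groups (160, 130 and 100 mg/dL) this is 8.3, 10.2 and 13.3 percentage points. Randomized subjects have not reached their goal, so these are the largest values for each group, not typical ones. One absolute number does not define one percentage margin, and the document gives no SD on the percentage scale.

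**The case against.** Several objections limit how far the point can be pushed.

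- **No passage says that a nonsignificant result will be called noninferior.** A reader might infer it, because no other rule is offered, but the documents do not state it. The 20% is the cost of that reading, not a property of a stated rule.
- **The analysis model is sound for the purpose.** The primary-endpoint wording, "by comparing the treatment effect to that of the active control group", is neutral, and the mixed model yields a week-12 estimate and interval. A two-sided 95% interval corresponds to a one-sided 0.025 test, so two-sidedness is not a fault. Difference tests also suit the superiority hypotheses on safety and adherence. It would be too strong to say that every test is the wrong kind.
- **Smaller deficits are not errors against a 0.343 margin.** A difference test is nonsignificant 63% of the time at a deficit of 0.2 and 87% at 0.1, and one might quote these as false acceptances. Both deficits lie inside 0.343, and the confidence-limit rule would itself accept them about 21% and 51% of the time.
- **The origin of 0.343 cannot be judged here.** The source study is said to have "examined effects of medicinal cake-separated moxibustion with different dosage upon blood fat and hemorheology in patients with hyperlipemia". One might conclude that it tells nothing about simvastatin's effect, but the description does not say whether it had a statin arm, and the study is not available. 0.343 may have been meant as the margin.
- **The choice of the full analysis set is partly covered.** Crossover and stopping treatment might pull the arms together, but stopping acupuncture could also widen the gap, and the completer analysis is already planned.

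What remains is that neither a margin nor a decision rule is stated.

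**Conclusion.** The point holds as a missing margin and missing decision rule for the declared primary hypothesis, and it should be settled before results are known. The model, alpha and analysis sets can stay.

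The size, about 20% against 2.5% acceptance of a deficit of 0.343, rests on the plan's SD and 65 per arm, a normal approximation on the absolute scale, and the supposition that nonsignificance is read as noninferiority.

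A reader might also infer that the repair needs no extra patients. The documents support that only for a margin of about 0.343 or wider on the absolute scale. On the percentage scale the power cannot be computed from what is given.

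**What to change.** Before unblinding of the database:

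1. State one margin for the primary endpoint in percentage points and justify it.
2. State the rule: conclude noninferiority only if the upper limit of the two-sided 95% confidence interval for acupuncture and moxibustion minus simvastatin, in week-12 percentage change in LDL-C from the planned mixed model, lies below that margin.
3. Report the same interval in the completer set and look for a consistent conclusion.
4. For secondary efficacy outcomes, claim noninferiority only where a margin is named; otherwise report differences with 95% confidence intervals.
5. Say whether 0.343 was the intended margin. If so, give its unit, its conversion to the percentage scale and its justification.
6. Restate the power of 65 per arm for the chosen margin, with an SD on the percentage scale.

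The cost is wording, a justification of the margin and a fresh power calculation. The downside is that the stated power may become less favourable: on the absolute scale it is about 80% at 0.343 but about 53% at an assumed 0.25.

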#### Statistical analysis plan

The primary analysis set for the primary endpoint is the FAS. It is to use the repeated measures, linear mixed-effects model, including terms for treatment group, stratification factor, baseline LDL-C, scheduled visit and the interaction of treatment with scheduled visit. Missing values will not be imputed when the repeated measures, linear mixed-effects model is used.

We will use the chi-squared test for binary outcomes, and the *t* test for continuous outcomes. For subgroup analyses, we will use regression methods with appropriate interaction terms (respective subgroup treatment group). Multivariable analyses will be based on logistic regression for binary outcomes and linear regression for continuous outcomes. We will examine the residual to assess model assumptions and goodness-of-fit. For timed endpoints, such as mortality, we will use the Kaplan-Meier survival analysis followed by the multivariable Cox proportional hazards model for adjusting for baseline variables. We will calculate Relative Risk (RR) and RR Reductions (RRR) with corresponding 95% confidence intervals to compare dichotomous variables, and difference in means will be used for additional analysis of continuous variables. *P* values will be reported to four decimal places with *P* values < 0.05 reported as *P* < 0.05. Up-to-date versions of R (R Foundation) will be used to conduct analyses. For all tests, we will use two-sided *P* values with alpha no greater than 0.05 level of significance. We will use the Bonferroni method to appropriately adjust the overall level of significance for multiple primary outcomes, and secondary outcomes.

In investigation of the robustness of the analysis results, the primary analysis will be repeated using the CAS. In addition, parametric analysis of covariance (ANCOVA) and appropriate nonparametric methods will be used on the FAS, in which missing data will be imputed using the last-observation-carried-forward (LOCF) approach. The primary analysis will also be repeated for subgroups of interest.

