### Outcome measurements

#### Primary outcome

The primary outcome is the percentage change from baseline to the end of the study (after the 12-week intervention and after another 4-week follow-up) in LDL-C. The calculated LDL-C concentration will be determined at screening (entry to the study), day 1 (after TLC is completed and eligibility is determined), week 6, and week 12. LDL-C will be measured by preparative ultracentrifugation by the central laboratory. The LDL-C concentration calculated at screening will be reported only for the eligibility decision. The baseline lipid measurements for the purpose of analysis will be the day-1 lipid measurement after TLC (lipid stabilization). This will be collected after a ≥9-h fast and before receiving intervention.

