### Lipid Measurements

The baseline lipid measurements for the purpose of analysis will be the central laboratory screening and day 1 lipid measurement collected after a ≥ 9 hour fast and before receiving intervention. At each time points, calculated LDL-C concentration will be determined. In addition, at screening, day 1, week 6, and week 12 LDL-C will be measured by preparative ultracentrifugation by the central laboratory. Only the screening calculated LDL-C concentration will be reported to the site for the eligibility decision. For subjects who are rescreened, data from the first screening period will not be used for the analysis. Investigators, subjects, and the study team will be blinded to post-randomization central laboratory lipid panel values for the duration of the study until unblinding of the database. In addition, investigators and staff involved with this trial and all medical staff involved in the subject’s medical care should refrain from obtaining lipid panels between randomization and at least 4 weeks after the subject ends the study at week 12 (to avoid potential unblinding). If a lipid panel is drawn, all reasonable steps must be undertaken to avoid informing the subject and study personnel of the results.

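### The primary model has one baseline LDL-C term, the protocol defines that baseline in two ways, and the screening LDL-C could be prespecified as a second covariate for a small gain in precision

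*Protocol article*

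**What the plan says.** All references are to the Protocol article.

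- **Model.** The Statistical analysis plan section sets out the repeated-measures mixed model for the primary endpoint on the full analysis set, "including terms for treatment group, stratification factor, baseline LDL-C, scheduled visit and the interaction of treatment with scheduled visit". There is one LDL-C covariate.
- **Baseline, main text.** Primary outcome says: "The baseline lipid measurements for the purpose of analysis will be the day-1 lipid measurement after TLC (lipid stabilization". It adds: "The LDL-C concentration calculated at screening will be reported only for the eligibility decision".
- **Baseline, appendix.** Lipid Measurements in Appendix 2 says: "The baseline lipid measurements for the purpose of analysis will be the central laboratory screening and day 1 lipid measurement". It does not say whether the two values are averaged, entered separately, or used for different purposes.
- **Availability.** Inclusion criteria require a central-laboratory fasting LDL-C for entry. Appendix 2 states that "at screening, day 1, week 6, and week 12 LDL-C will be measured by preparative ultracentrifugation by the central laboratory". Both readings precede allocation, because Trial design has the diet period first: "After TLC is completed, subjects who have not reached the target lipid level will be randomly assigned".
- **Sizing.** Sample size uses an effect of 0.343 and a standard deviation of 0.7 on absolute LDL-C change and arrives at 65 per group.

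**The concern.** There are two linked questions. First, the covariate called baseline LDL-C is not uniquely defined. By the main text it is the day-1 value; by Appendix 2 it involves screening as well. An analyst could not tell from the document what to do with the screening value.

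Second, a single fasting LDL-C is a noisy reading of a subject's level, and in a percentage change the day-1 value is also the denominator. A second pre-randomization reading, already collected for everyone, can carry information about the underlying level that the day-1 reading misses. Using it as a covariate cannot bias a randomized comparison. A noninferiority conclusion rests on the width of a confidence interval, and the stated sample size leaves no reserve, so even a small reduction in residual variance is worth having if it costs nothing. What is at stake is precision, not validity.

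**Working it through.** **1. Reproduce the plan's sample size.** Inputs from Sample size: difference 0.343, SD 0.7, power 0.80. The text "A significance level of 0.95 and a power of 0.80 will be allocated for the calculation of sample size" is read as alpha 0.05, two-sided, in line with "we will use two-sided *P* values with alpha no greater than 0.05 level of significance".

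n per arm = 2 × [0.7 × (1.960 + 0.842) / 0.343]² = 65.4, against 65 stated. The figure reproduces to within rounding.

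Power at 65 per arm = Φ(0.343 / (0.7 × √(2/65)) − 1.960) = Φ(2.793 − 1.960) = 0.798. The t-based value is 0.792. The nominal calculation therefore sits at its target with nothing to spare.

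**2. Bounds on the gain from a second baseline.** Let f be the residual variance with day 1 and screening in the model, divided by the residual variance with day 1 only. The document gives no correlations, so these are assumed.

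- *Equal correlation ρ among screening, day 1 and week 12:* f = [1 − 2ρ²/(1 + ρ)] / (1 − ρ²). For ρ = 0.3, 0.5, 0.7 and 0.8, f = 0.947, 0.889, 0.830 and 0.802.
- *Correlation decaying with time, screening to week 12 equal to ρ²:* f = 1.00, so no gain.
- *Halfway between, ρ from 0.5 to 0.8:* f = 0.972 to 0.951.

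These formulas leave out the risk stratum, the diet period and the two selections on LDL-C. The large gains under equal correlation should not be expected here.

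**3. Simulations closer to the design.** Subjects fall in three strata with thresholds 160, 130 and 100 mg/dL and are kept only if at or above threshold at both screening and day 1. The stratum is in both models, and the outcome is week-12 percentage change.

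- With between-subject and within-subject SDs of (28, 15), (28, 20) and (25, 25) mg/dL and a diet effect of 5%: f = 0.935, 0.943 and 0.962, a reduction of 3.8% to 6.5%.
- On the log scale, with between-subject SD 0.15–0.20, within-subject SD 0.07–0.10, diet-response SD 0.04–0.08 and treatment-response SD 0.08–0.14, over 16 parameter sets: a reduction of 2.1% to 10.1%.

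Allowing for other plausible inputs, the range is roughly 1% to 10%, with most settings at 3% to 7%. The decaying-correlation case shows that it can approach zero.

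**4. What that buys.** The interval narrows by 1 − √f. Nominal power at 65 per arm is Φ(2.793/√f − 1.960). The equivalent number of extra subjects is 130 × (1/f − 1).

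| f | CI narrower by | Power, normal | Power, t | Extra subjects |
|---|---|---|---|---|
| 1.00 | 0 | 0.798 | 0.792 | 0 |
| 0.97 | 1.5% | 0.810 | 0.804 | 4 |
| 0.95 | 2.5% | 0.818 | 0.812 | 7 |
| 0.93 | 3.6% | 0.826 | 0.820 | 10 |

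**The case against.** The strongest case against is that nothing here is wrong. A mixed model with treatment, stratum, one baseline value, visit and treatment by visit is standard, keeps its type I error, and already takes the main covariate gain. Further prognostic covariates are often left to an analysis plan that is not shown. The first part stands in full and is why the point is an efficiency suggestion. The second part stands only in part: the article itself fixes the model terms, and it contradicts itself on what the baseline is.

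Several stronger readings are tempting, and the document does not support them.

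- *That the plan settles on day 1 alone and discards the screening value.* Appendix 2 names both values as the analysis baseline, so the matter is unresolved.
- *That the main text bars analytic use of screening LDL-C.* The sentence on reporting for eligibility is most naturally a disclosure rule. Appendix 2 gives the fuller version, which limits what the site is told, next to the blinding provisions.
- *That screening is an independent second reading of the same level.* A diet, weight and activity programme lies between the two readings, subjects are selected on LDL-C at both, and the stratum, tied to the entry thresholds, already carries part of the information. It is a separate reading, not a replicate.
- *That the power of the planned analysis is shown to be marginal.* The SD of 0.7 is for absolute change with no adjustment mentioned, while the primary endpoint is percentage change from an adjusted model. The power figures carry a variance ratio over to that SD and are nominal only.

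Against the objection, the zero-gain case requires the day-1 reading to contain everything that screening tells about week 12. With any within-subject or assay error in one reading, that is a limiting case rather than the expected one. The simulations already include the stratum and both selections.

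**Conclusion.** The point holds as a low-severity efficiency improvement with one firm textual element. The firm element is that the main text and Appendix 2 define the analysis baseline differently, and neither says how screening LDL-C enters a model that has one baseline term. The efficiency element is that prespecifying screening LDL-C as a second covariate is valid and nearly free. It would most likely cut residual variance by about 3% to 7% (plausible range roughly 1% to 10%, possibly near zero). At 3% to 7% the interval narrows by 1.5% to 3.6% and nominal power rises by 1 to 3 points from about 79% at 65 per arm. All of these sizes rest on assumed variances and correlations and, for power, on the SD stated for absolute change. The existing model is not biased, and a result obtained from it would stand.

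**What to change.** 1. Reconcile Primary outcome with Lipid Measurements in Appendix 2: state that the day-1 value after the diet period is the sole baseline, and hence the denominator, for percentage change. Do not average it with screening, which would mix levels before and after the diet period.
2. In the Statistical analysis plan section, add screening LDL-C, measured by the same ultracentrifugation method as day 1, as a second fixed covariate in the primary mixed model, and specify this before any unblinded look at the data.
3. Optionally, do the same with the corresponding screening value for HDL-C, total cholesterol and triglycerides. No gain has been calculated for those endpoints.

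The cost is one line in the plan, one corrected sentence in the appendix and one degree of freedom. No new data are needed.

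### Both robustness analyses on the full analysis set use LOCF, which scores early dropouts as no LDL-C change and may give false reassurance about noninferiority

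*Protocol article*

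**What the plan says.** The Trial design section states: "This is a multicenter, open-label, randomized, stratified, active-controlled, noninferiority trial with two parallel groups". Under Statistical analysis plan, the primary analysis is a repeated-measures mixed model on the FAS, with baseline LDL-C as a covariate, and "Missing values will not be imputed when the repeated measures, linear mixed-effects model is used".

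The same section then names the robustness analyses. One repeats the primary model on the Completer Analysis Set (CAS). The others are ANCOVA and nonparametric methods on the FAS, for which "missing data will be imputed using the last-observation-carried-forward (LOCF) approach".

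Three other statements determine what LOCF does here:

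- Dataset analysis: a randomized subject enters the FAS after a single treatment. No post-baseline LDL-C is required.
- Primary outcome: after screening, LDL-C is listed at day 1, week 6 and week 12, and day 1 is the analysis baseline. Dataset analysis sets the primary comparison at week 12.
- Sample size: "we assume that 90% of subjects will remain in the study".

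**The concern.** A subject lost before week 6 has only the day-1 value to carry forward, which gives a percentage change of exactly zero. A subject lost after week 6 is held at the week-6 value. In both cases the analysis treats the filled-in value as an observation.

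Subjects with no post-baseline LDL-C contribute no outcome to the mixed model and are excluded from the CAS. The LOCF analyses are therefore the only ones named in the article that count them, and they count them as unchanged in either arm.

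In a superiority trial, pulling the arms together usually works against the claim. In a noninferiority trial it works for it: zeros in the simvastatin arm reduce the effect that acupuncture has to match. If LOCF agreed with the primary result, readers could take that as robustness when part of the agreement came from the imputation.

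**Working it through.** **The plan's own figure.** The Sample size section gives "an effect size of 0.343 on absolute value change of LDL-C value, and a standard deviation of 0.7" and says: "A significance level of 0.95 and a power of 0.80 will be allocated for the calculation of sample size". Reading the first figure as alpha 0.05, two-sided:

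n per arm = 2 × [0.7 × (1.960 + 0.842) / 0.343]² = 65.4

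This agrees with the stated 65 or so. A noninferiority calculation with margin 0.343 and one-sided 2.5% gives the same number; one-sided 5% gives 52 and does not reproduce it. The section's inflated figure of roughly 70 per arm is used below.

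**Inputs**

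- From the article: SD 0.7, 70 per arm, 10% loss, measurement times.
- Assumed: 0.343 is the noninferiority margin and also the true deficit of acupuncture. The article calls it an effect size, gives no unit and states no margin.
- Assumed: simvastatin lowers LDL-C by X = 0.7, 1.0 or 1.3 mmol/L; the week-6 effect equals the week-12 effect; within-subject correlation is 0.7; dropout is random within arm.
- Scale: absolute change, because the planning figures are absolute, although the primary endpoint is percentage change.

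**Expected LOCF difference.** With early dropout fractions dA (acupuncture) and dS (simvastatin), all scored as zero change:

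- acupuncture mean = −(1 − dA)(X − 0.343)
- simvastatin mean = −(1 − dS)X
- difference = (1 − dA) × 0.343 + (dA − dS) × X

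With equal dropout the second term vanishes and the difference shrinks by exactly the dropout fraction. LOCF becomes conservative only when (dA − dS) × X exceeds dA × 0.343, so acupuncture must lose clearly more subjects, not just slightly more.

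**Hand check for 10% in each arm.** Difference = 0.90 × 0.343 = 0.309, a shift of 0.0343. SE = 0.7 × √(2/70) = 0.1183. One-sided error ≈ Φ(0.0343/0.1183 − 1.96) = Φ(−1.67) ≈ 4.7%, against 2.5% nominal.

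**Simulation.** 8,000 trials per scenario, comparing arm means, with the 97.5% upper bound tested against 0.343. Ranges cover the three values of X.

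| Dropout, acupuncture / simvastatin | Expected LOCF difference | False noninferiority |
|---|---|---|
| 10% / 10%, all before week 6 | 0.309 | 4.2% to 5.2% |
| 10% / 10%, about half after week 6 | 0.95 × 0.343 = 0.326 | 3.1% to 3.4% |
| 20% / 20%, all before week 6 | 0.80 × 0.343 = 0.274 | 7.2% to 8.6% |
| 5% / 15%, all before week 6 | 0.326 − 0.10X = 0.256 to 0.196 | 11.6% to 21.0% |
| 5% / 15%, about half after week 6 | 0.334 − 0.05X = 0.299 to 0.269 | 5.3% to 8.5% |
| 15% / 5%, all before week 6 | 0.292 + 0.10X = 0.362 to 0.422 | 1.7% to 0.4% |
| Completers only, same dropout patterns | 0.343 | 2.2% to 2.8% |

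**The case against.** The strongest reply is that LOCF enters only supportive analyses. The primary model does not impute, and the CAS repeat does not depend on LOCF. This stands. A reader might infer that the primary noninferiority result is biased by LOCF; the article does not support that.

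A reader might also infer that LOCF always favours acupuncture, or that it can never test robustness. That is too strong. With 15% early loss on acupuncture and 5% on simvastatin it is conservative, and nothing in the article fixes which arm will lose more. The Background and Discussion describe statins as having poor compliance and frequent side effects, which makes heavier simvastatin loss plausible. Against this, the simvastatin section keeps subjects who stop the drug for intolerance in study visits and measurements, and the adverse-event withdrawal section encourages an end-of-study assessment. If followed, these provisions should limit missing values, although full withdrawal remains possible at any time.

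A larger error is tempting. If 10% of the simvastatin arm and nobody on acupuncture were lost early, with 65 per arm, the shift would be 0.10 × X = 0.07 to 0.13, the SE 0.7 × √(2/65) = 0.1228, and the error about 8% to 18%. The arithmetic is right, but this is 5% loss overall and all on one side. The article's 10% is used to enlarge both groups, so it is not the source of that scenario.

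Finally, a separate analysis plan, not shown, may contain a stress test. The absence of one from the article is therefore not the point. The point is the method the article names.

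**Conclusion.** The point holds in a limited form. Both alternative FAS methods use LOCF. It scores early losses as zero change, and the direction of the resulting bias depends on a dropout pattern that is not known in advance. Under the article's own 10% loss, equal and early, the effect is modest: a true difference of 0.343 appears as about 0.309, and one-sided error rises from 2.5% to about 4% to 5%. If half of the losses come after week 6, it is just over 3%. It becomes material, about 12% to 21%, only if early loss is clearly heavier on simvastatin.

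The direction under equal dropout follows from the algebra. The error rates rest on the assumed margin, simvastatin effect and dropout timing, and on the absolute scale. The consequence is possible false reassurance from a supportive analysis, not an invalid primary analysis. It should be corrected because the change is cheap and the named method is a poor test of a noninferiority claim.

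**What to change.** In the Statistical analysis plan section, replace LOCF for the FAS robustness analyses with multiple imputation done separately by arm, using day-1 LDL-C, week-6 LDL-C and risk stratum. Add a delta adjustment that worsens the imputed acupuncture values in steps until noninferiority is lost, and report that tipping point. Run the ANCOVA on these data sets; if the nonparametric analysis is kept, run it on the same ones.

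The delta step is the essential part. Imputation under missing-at-random alone would largely repeat the assumption already made by the primary mixed model.

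The cost is a change of wording before unblinding and modest extra programming in R. No new data, visits or subjects are needed, and the sample size does not change.
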